#### Participants

This study is a multicenter, prospective, observational study. Subject recruitment was started in 2018 and is ongoing. Participants are being recruited at seven hospitals and three outpatient clinics in Japan. Patient recruitment is being conducted at the following locations and hospitals: Tokyo (Keio University Hospital, Tsurugaoka Garden Hospital, Oizumi Hospital, Komagino Hospital, Oizumi Mental Clinic, Asakadai Mental Clinic), Kanagawa (Nagatsuta Ikoinomori Clinic), Shiga (Biwako Hospital), Yamagata (Sato Hospital), and Fukushima (Asaka Hospital). Participants are inpatients or outpatients aged ≥20 years who meet the diagnostic criteria for depression, bipolar disorder, schizophrenia, anxiety disorder (including obsessive-compulsive disorder), mild cognitive impairment, or dementia according to the DSM-5 or ICD-11. Healthy volunteers will consist of healthy individuals with no history of psychiatric disorders who have volunteered to participate in the study after reading the research group's website and printed recruitment advertisements and who are at least 20 years old at the time of consent. Researchers will obtain written informed consent about participation in this study and data storage from all the participants. In cases where the patients are judged to be decisionally impaired, the patients' guardians will be asked to provide consent. Participants will be able to leave the study at any time. This study was approved by the Institutional Review Board of Keio University School of Medicine and the participating medical facilities.

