##### Clinical assessment

The severity of the illness will be assessed using the rating scales described in the table (Table 1). In addition, the treating psychiatrists will be asked to evaluate each patient's current disease severity using the Clinical General Impression Scale-Severity (CGI-S). A structured psychiatric diagnostic interview (SCID-IV-TR) will be conducted to the greatest degree feasible to confirm the diagnoses during the follow-up interview.

**Table 1 T1:** Data collection and visit schedule.

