In this study, not only the collection of linguistic information associated with each disease but also the relationship between illness severity and linguistic information will be important. Therefore, we will follow the participants two to five times during the study period to interview the subjects at times when the severities of their symptoms differ (i.e., severe, moderate, mild, and during remittance). An interval of at least 1 month between the two assessments will be required. The same procedures described above will be conducted for the follow-up data collection.

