#### Data processing and annotation

The acquired voice data will be converted into text information using speech recognition technology developed by the research group and will be compensated manually; annotations, such as pauses, fillers, nods, interjections, repetitions, co-supplementation, lexical responses, incomplete sentences, misstatements, etc., will also be made. We will mask the part of personal identifiers such as names when converting voice data into text information. At the same time, the following phonic information will be extracted from the recorded audio data to utilize the physical properties of the audio data in the machine learning model: fundamental frequency (F0); first, second, and third formant frequencies (F1, F2, F3); cepstral peak prominence (CPP); and Mel-frequency cepstrum coefficients (MFCC). These are the major features in speech-language analysis (40). Software such as Praat (41) and openSMILE (42) will be used to extract such phonic information.

Based on the annotated text data thus obtained, various variables are calculated using NLP techniques, such as morphological and syntactic analyses using MeCab (43, 44) and JUMAN (45, 46). For instance, these analyses will include the frequency of the occurrence of each part of speech, vocabulary (negative and positive words), syntactic complexity, length of the utterance, frequency of occurrence of person, use of pronouns and distance to the referent, use of case structure (“te, ni, wo, ha”), and so on. We will use NLP techniques to represent textual data as n-grams and word embeddings obtained from pre-trained models such as BERT (47).

Linguistic features considered to be characteristic of specific psychiatric diseases will be selected and statistically compared between groups (e.g., patients vs. healthy subjects, patients in different disease groups). This step is necessary to verify whether each variable has pathological validity before using it for machine learning.

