### Machine learning

The machine learning models in this study will be trained to perform the following tasks: (1) to predict whether a subject has or does not have psychiatric disorders such as depression, bipolar disorder, anxiety disorder, schizophrenia, or dementia; (2) to predict the severity of a subject's state based on the results of rating scales such as the Hamilton Rating Scale for Depression (HAM-D), the Young Mania Rating Scale (YMRS) for bipolar disorder, the Positive And Negative Syndrome Scale (PANSS) for schizophrenia, and MMSE for dementia; (3) to predict the improvement or deterioration of a subject's disorder with respect to a previously recorded state if the subject has undergone a prior assessment; and 4) to predict the scores of individual items in clinical rating scales that are indicators of different aspects of a subject's disorder, such as positive symptoms, negative symptoms, and disorganized symptoms for schizophrenia. The data used to train these machine learning models may include voice features extracted from voice data obtained from subjects, conversational and linguistic information from transcribed text data, and annotations assigned to the data described above.

Next, we will need to perform feature engineering and design the architecture of machine learning. The data, represented through NLP techniques, together with the features obtained through feature engineering processes, will be then used to extract disease features. In particular, disease features extraction will be performed relying on machine learning models such as decision trees, support vector machines (SVM), and deep learning architectures. Each model will be evaluated using cross-validation and then the relative importance of each feature will be estimated using a feature importance estimation method such as XGBoost. We will then evaluate the results using the mean absolute error, coefficient of determination, and correlation coefficients. We also plan to verify whether the features obtained in this manner can distinguish firstly between a normal and disease state, secondly among different diseases, and whether they can distinguish changes in disease severity over time.

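### Disease-versus-disease contrasts are planned by diagnosis alone on records of mixed severity and mood phase, so a marker of current state may be reported as a marker of disease

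*Protocol article*

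**What the plan says.** All references are to the protocol article.

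- **Participants.** Recruitment covers both care settings: "Participants are inpatients or outpatients aged" 20 years or over.
- **Clinical assessment, text after Table 1.** Each participant is seen two to five times, and the aim is to "interview the subjects at times when the severities of their symptoms differ (i.e., severe, moderate, mild, and during remittance").
- **Data processing and annotation.** Candidate features are to be "selected and statistically compared between groups (e.g., patients vs. healthy subjects, patients in different disease groups"). The section adds: "This step is necessary to verify whether each variable has pathological validity before using it for machine learning".
- **Machine learning.** The features are then tested on whether they "can distinguish firstly between a normal and disease state, secondly among different diseases", and separately on "whether they can distinguish changes in disease severity over time". Severity also appears as a prediction target, with HAM-D, YMRS, PANSS and MMSE given as examples for different diagnoses.
- **Clinical assessment.** Treating psychiatrists rate each patient's "current disease severity using the Clinical General Impression Scale-Severity (CGI-S"), and the same procedures are repeated at follow-up. This is the one severity measure requested for every patient group. No disease-versus-disease comparison or model in the article is said to use it.
- **Table 1.** Among patients, HAM-D, MADRS and YMRS are listed only for depression, bipolar disorder and anxiety disorder.
- **Sample size.** Variability in severity is one of the reasons given for multiplying the minimum sample about tenfold.

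**The concern.** The study wants biomarkers that help to diagnose, including telling one disease from another. Two diagnostic groups can differ in speech because the diseases differ, or because one group was recorded more often when severely ill, or in a different mood phase. A comparison by diagnosis alone cannot separate these explanations. As written, a group difference at the screening step counts as evidence of pathological validity, and the feature then goes forward to the classifier.

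The article itself supplies the mechanism. Its Introduction names flight of ideas in mania and psychomotor inhibition in depression as known speech features, and both depend on current state. Its severity-prediction tasks presuppose that features move with severity.

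The contrast most exposed is bipolar disorder against depression. YMRS is the example severity target for bipolar disorder, so manic records are anticipated there, while records in the depression group are not expected to be manic. Separation in that contrast could reflect mania against depression, which says little about the harder question of bipolar depression against unipolar depression. The differential-diagnostic value of the features would then be overstated.

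**Working it through.** **1. The plan's own figures.** Ten cases for each of about 100 variables gives 10 × 100 = 1,000, which matches the stated target. The other route, ten times the minimum of 50, gives 500. Neither calculation addresses imbalance of severity between diagnoses.

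**2. Inputs from the document.** Group sizes at September 2022 (Discussion): schizophrenia 102, depression 89, bipolar disorder 58, anxiety disorder 35, neurocognitive disorder 79, in total 363.

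**3. Assumed inputs.** The document gives no severity distribution by diagnosis and no correlation between features and severity. Assumptions: one record per patient; severity S with SD 1 in each group; a gap of d SD in mean severity between two diagnoses; and a marker with no disease effect at all,

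M = r·S + √(1 − r²)·e, with e standard normal.

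The within-group SD of M is then 1 and the difference in group means is r·d. S can equally be read as a mood-state axis.

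**4. Apparent discrimination.** AUC = Φ(r·d/√2).

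| d | r = 0.5 | r = 0.7 |
|---|---|---|
| 0 | 0.50 | 0.50 |
| 0.5 | Φ(0.177) = 0.57 | Φ(0.247) = 0.60 |
| 1.0 | Φ(0.354) = 0.64 | Φ(0.495) = 0.69 |

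The formula contains no sample size. More records estimate the same misleading AUC more precisely. Cross-validation does not help, because the same imbalance sits in training and test folds.

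**5. Chance of passing the group-comparison screen.** For a two-sided 5% test, the rejection probability is about Φ(r·d/√(1/n₁ + 1/n₂) − 1.96). At r = 0.5 and d = 0.5 the mean difference is 0.25.

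- Bipolar disorder 58 v anxiety disorder 35: Φ(0.25/0.214 − 1.96) = 21%.
- Depression 89 v bipolar disorder 58: Φ(0.25/0.169 − 1.96) = 32%.
- Schizophrenia 102 v depression 89: Φ(0.25/0.145 − 1.96) = 41%.

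The same marker and the same gap give more false findings as the groups grow. At d = 1 and r = 0.5 the three figures are 65%, 84% and 93%.

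**6. Effect of conditioning.** Simulation with 2,000 runs, schizophrenia 102 v depression 89, r = 0.5:

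| d | Unadjusted | Severity as covariate |
|---|---|---|
| 0 | 4% | 5% |
| 0.25 | 14% | 5% |
| 0.5 | 39% | 5% |
| 0.8 | 78% | 6% |

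Adjustment restores roughly the nominal rate when severity is measured on one common scale without error. CGI-S is a rating with error, so in practice some confounding would remain.

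**The case against.** The strongest reply is that this is silence and not error. A condensed article leaves covariates, strata and matching to a fuller plan, it names no test for the group comparison, and nothing in it says that the contrasts are unadjusted. That is a fair limit: an adjustment may exist elsewhere. But the article goes further than silence. It states how a between-group difference is to be read, and the remedy it offers for severity variability, a larger sample, deals with noise and not with confounding.

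A reader might infer that a severity or phase marker will be reported as disease-specific. The documents do not support that. Bias needs an unequal mix of states between diagnoses, and no such distribution is given. Mixed severity that is equal across groups adds noise but no false disease signal. Following patients through several states may even bring the groups closer together than a single recording would.

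A reader might also infer that severity is ignored. It is not. It is modelled as a separate task, the same features are checked against change over time, and the list of severity scales is open, so it does not rule out CGI-S. That check could expose a state marker. What is missing is any rule linking its result to a claim of disease specificity.

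Finally, severity and phase can be part of the disease, so conditioning on them may remove real signal and changes the question asked. This stands, and it is why conditioned analyses should supplement the planned contrasts and not replace them.

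**Conclusion.** The point holds as a risk that the plan leaves open. Following the two sections as written can pass a pure state marker as a diagnostic one if the severity or phase mix differs between diagnoses. The size depends wholly on that mix. With assumed correlations of 0.5 to 0.7, the spurious AUC is 0.57 to 0.60 at a 0.5 SD gap and 0.64 to 0.69 at 1 SD; it is 0.50 with no gap. Larger gaps would give larger values, but nothing in the document supports a particular gap. For bipolar disorder versus depression an imbalance of phase follows once manic records are included, although the article does not say how many there are or how phases are pooled. The matter should be addressed before disease-versus-disease results are interpreted; it does not undermine the dataset or the severity tasks.

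**What to change.** Keep the planned contrasts and put a state-conditioned analysis beside each.

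- **All disease-versus-disease contrasts.** Show the CGI-S distribution by diagnosis. Repeat the feature comparison and the classifier within CGI-S bands or adjusted for CGI-S, and compare a CGI-S-only model with one that adds the speech features.
- **Bipolar disorder versus depression.** Add a contrast of bipolar records with low YMRS against depression records in the same HAM-D/MADRS range, with the cut-offs fixed beforehand.
- **Reporting rule.** Describe a feature as disease-specific only if the separation persists in these analyses. Otherwise report it as possibly reflecting current state.

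The cost is analysis work only, since CGI-S, HAM-D, MADRS and YMRS are already collected. The downsides are fewer records per contrast, possibly lower accuracy, and the chance of adjusting away true disease signal tied to severity. Matching on mood phase is limited to the patient groups for which Table 1 lists the mood scales; it cannot extend to the schizophrenia or neurocognitive groups, where CGI-S has to serve.

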##### Demographic characteristics

Sex, age, diagnosis, diagnosis subtype, duration of illness, prescription, and complications will be collected from the medical records. We will also collect as much information as possible about their education, birthplace, outpatient or inpatient status, years of education, educational background, occupation, work status, employment status, income, marital status, number of years of married (or divorced or separated), number of children, number of people living together, etc. If some information is missing, the patients will be asked to provide the information.

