			**Number of visits**				
			**1**	**2**	**3**	**4**	**5**
			**Assessments must be done in Visit 1 and Visit 2**		**Assessments will be done as long as possible**		
A) Demographic characteristics	All participants	Demographic characteristics	✓				
		Information on treatment history	✓	✓	✓	✓	✓
	Only patients	SCID-IV-TR	✓ (Once during research period)				
B) Conversation with a psychiatrist or psychologist	All participants	free conversation, picture-description task, and story-telling task	✓	✓	✓	✓	✓
C) Severity assessment using clinical rating scales	C-1) Monopolar depression disorder or Bipolar disorder or Anxiety disorder	HAM-D MADRS YMRS HAM-A STAI SWLS Cantril's Ladder of life scale FS-J Subjective Well-being Inventory	✓	✓	✓	✓	✓
	C-2) Schizophrenia	PANSS SWLS Cantril's Ladder of life scale FS-J Subjective Well-being Inventory	✓	✓	✓	✓	✓
	C-3) Neurocognitive disorder	MMSE CDR MoCA-J WMS-R LM SWLS Cantril's Ladder of life scale FS-J Philadelphia Geriatric Center Morale Scale Subjective Well-being Inventory	✓	✓	✓	✓	✓
	For healthy volunteers	*MMSE (*: Performed before all of the other tests)	✓				
		All of C-1), C-2), C-3)	✓	✓	✓	✓	✓

FS-J, The Japanese version of the Flourishing Scale; SWLS, Satisfaction With Life Scale, SCID, Structural Clinical Interview for DSM-5; HAM-D, Hamilton Depression Rating Scale; MADRS, Montgomery-Asberg Depression Rating Scale; YMRS, Young Mania Rating Scale; STAI, State-Trait Anxiety Inventory; PANSS, Positive And Negative Syndrome Scale; MMSE, Mini-Mental State Examination; MoCA-J, Montreal Cognitive Assessment-Japanese version; WMS-R LM, Wechsler Memory Scale-Revised Logical Memory; CDR, Clinical Dementia Rating; M.I.N.I., Mini-International Neuropsychiatric Interview.

Healthy volunteers will be screened using the Mini-International Neuropsychiatric Interview (M.I.N.I.) and the Mini-Mental State Examination (MMSE). They will be excluded if they have a history of psychiatric disorders or cognitive impairment. For the M.I.N.I., if any diagnosis is found, and for the MMSE, if the score is below 27, the participant will not be allowed to participate in the study as a healthy subject.

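### The severity and change models are evaluated without the treatment information collected at every visit, so a treatment effect on speech could be reported as a marker of severity

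*Protocol article*

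**What the plan says.** **Sampling.** The Clinical assessment section, in the text below Table 1, gives the relation between severity and language as the reason for two to five visits. It plans to "interview the subjects at times when the severities of their symptoms differ". On timing it adds only this: "An interval of at least 1 month between the two assessments will be required". The Participants section calls the study observational.

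**Treatment data.** The Demographic characteristics section states: "Sex, age, diagnosis, diagnosis subtype, duration of illness, prescription, and complications will be collected from the medical records". Table 1 ticks the demographic row at visit 1 only. A separate row, "Information on treatment history", is ticked for all participants at visits 1 to 5.

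**Models.** The Machine learning section sets four tasks. Task 2 predicts severity on rating scales, task 3 is "to predict the improvement or deterioration of a subject's disorder with respect to a previously recorded state", and task 4 predicts individual scale items. On inputs it says: "The data used to train these machine learning models may include voice features extracted from voice data obtained from subjects", followed by "conversational and linguistic information from transcribed text data, and annotations assigned to the data described above". Evaluation is by cross-validation, with mean absolute error, coefficient of determination and correlation. The features are then to be checked for "whether they can distinguish changes in disease severity over time". Treatment does not appear in this section as an input, comparator, stratum or sensitivity analysis.

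**The concern.** Severity is made to vary by design, and treatment is left free to vary with it. A drug that slows speech or alters the voice could move pauses, fillers or fundamental frequency. If its use also rises or falls with the rating scale, the feature will follow the scale even where the illness itself has no effect on that feature. The stated evaluation would credit the feature to the disorder.

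This matters because the Aim is an objective biomarker for assessing severity, which claims more than prediction of a score. A feature that reflects treatment may not carry over to patients treated differently. The issue lies within a disorder (tasks 2 and 4) and within a patient (task 3). It is separate from the comparison of patients with healthy volunteers.

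**Working it through.** **The plan's own figure.** Sample size section: 10 cases per variable × about 100 variables = 1,000. This reproduces and is not in dispute.

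**Inputs from the article.** Patients so far (Discussion): 102 schizophrenia, 89 depression, 58 bipolar, 35 anxiety, 79 neurocognitive; 102 + 89 + 58 + 35 + 79 = 363.

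**Inputs assumed.** r = correlation of treatment (or its change) with severity (or its change). b = correlation of treatment with a speech feature. The article gives neither, so a range is used.

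**Step 1: size of the spurious correlation.** If the feature is linked to severity only through treatment, the apparent correlation is r × b, and the partial correlation given treatment is 0.

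- 0.3 × 0.3 = 0.09
- 0.5 × 0.6 = 0.30
- 0.6 × 0.7 = 0.42
- r = 0 gives 0, so there is no bias without a link between treatment and severity.

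**Step 2: how firm it would look within one disorder.** Fisher z for 0.30 is 0.3095, with standard error 1/√(n − 3), taking one visit pair per patient.

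- Schizophrenia, n = 102: 1/√99 = 0.1005; 0.3095 ± 1.96 × 0.1005 = 0.1125 to 0.5065; back-transformed, 0.11 to 0.47.
- Anxiety, n = 35: 1/√32 = 0.1768; 0.3095 ± 1.96 × 0.1768 = −0.037 to 0.656; back-transformed, −0.04 to 0.58.

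The spurious value would exclude zero in the largest group but not in the smallest.

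**Step 3: chance that one such feature reaches two-sided p < 0.05 in schizophrenia (n = 102).**

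| r | b = 0.3 | b = 0.5 |
|---|---|---|
| 0 | 5% | 5% |
| 0.2 | 9% | 17% |
| 0.4 | 22% | 52% |
| 0.6 | 44% | 87% |

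**Step 4: does cross-validation catch it?** This was simulated with ten features that have no direct effect of severity, a linear model, 5-fold cross-validation and 300 repetitions. The table gives the mean cross-validated correlation with severity when treatment is left out.

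| r | b | n = 102 | n = 363 |
|---|---|---|---|
| 0 | 0.3 | −0.03 | −0.03 |
| 0 | 0.5 | −0.05 | −0.03 |
| 0.2 | 0.3 | 0.00 | 0.07 |
| 0.2 | 0.5 | 0.03 | 0.09 |
| 0.4 | 0.3 | 0.13 | 0.22 |
| 0.4 | 0.5 | 0.23 | 0.30 |
| 0.6 | 0.3 | 0.29 | 0.38 |
| 0.6 | 0.5 | 0.42 | 0.50 |

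Cross-validation does not catch it, because the same treatment–severity link is present in the training and test folds. A comparison with a treatment-only model does. Adding the speech features changed R² by −0.10 to −0.16 at n = 102 and by −0.02 to −0.04 at n = 363, so they gave no gain in any scenario. The n = 363 column shows only that more data does not remove the effect. The real disorders are scored on different scales and would not be pooled in this way.

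**Step 5: does another stated check catch it?** The validity check at the end of the Data processing and annotation section compares diagnostic groups. It does not address treatment that varies within a disorder or a patient.

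**The case against.** **Treatment is not excluded.** The input list is permissive ("The data used to train these machine learning models may include voice features extracted from voice data obtained from subjects"), and feature engineering and architecture are still to be designed. A full protocol or SAP, not shown, may deal with treatment. This stands: a reader might infer that the plan rules treatment out, and the text does not support that. The point is narrower. The article itself sets the sampling, the metrics and the wording of the conclusion, and as stated they cannot separate treatment from severity. Adding treatment as one more predictor would not do so either unless the gain from speech is shown.

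**The premise is assumed.** A reader might infer that doses do follow severity in this study. No section says so. Treatment information at every visit suggests that treatment is expected to vary, but not in which direction or how strongly. The supported wording is therefore that a treatment effect can be reported as a marker, not that it will be.

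**Precision is easy to overstate.** About 1,000 records less 400 first visits gives roughly 600 follow-up pairs, and at that number 0.30 would have an interval of about 0.23 to 0.37. The documents do not support using it. The pairs would mix healthy volunteers with disorders rated on different scales, and would treat repeated pairs from one person as independent.

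**Harm to early detection.** A reader might infer that such a marker would fail or reverse in untreated people. The article gives no basis for that, and detecting disorder is task 1, which is not at issue here.

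**A strict remedy could reject valid markers.** If treatment follows severity, it is partly a proxy for severity, so demanding a gain over treatment penalises a true marker. Pairs with unchanged prescription may also span less change in severity. This stands, and it rules out an automatic exclusion rule.

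**The data are largely scheduled already.** True. On collection, only a clarification of Table 1 is needed.

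**Conclusion.** The point holds as a proportionate improvement. The plan makes severity vary within patients, schedules treatment information at every visit, and states an evaluation for tasks 2 to 4 that does not use it, while wording the conclusion as disease severity. Over the assumed range, the spurious correlation runs from 0.09 to 0.42 and is zero if treatment is unrelated to severity. A value of 0.30 in schizophrenia would carry an interval of about 0.11 to 0.47. The size rests wholly on assumed correlations, linear relations and one visit pair per patient. That cross-validation cannot expose the effect follows from the link being the same in every fold and does not depend on the particular values.

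**What to change.** 1. **Table 1 and the Demographic characteristics section:** make clear that the every-visit treatment row includes the current drugs and daily dose at the time of each recording.
2. **Machine learning section, tasks 2 to 4:** report each speech model, by disorder, beside a treatment-only comparator and the combined model. For task 3 the comparator uses the change in treatment between visits.
3. **Task 3:** also report performance, with its interval, in visit pairs with unchanged prescription.
4. **Interpretation:** call items 2 and 3 sensitivity analyses that qualify how the severity claim is worded, with no automatic exclusion of features. State as limits that dose may be a proxy for severity, and that the unchanged-prescription subset is smaller and may span less severity change.

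**Cost.** Prescriptions must be coded across more than 1,000 records and five diagnostic groups. Each task gains a comparator and a combined model, and task 3 gains a subset. Subset estimates will be less precise, and headline performance may look less favourable. No new visits are needed, and no change to any patient's treatment is implied.
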